### 2.1.3 Design

Single blinded, randomised, controlled intervention trial..

### 2.1.4 Patient Selection and Inclusion/Exclusion Criteria

one hundred patients with type 2 diabetes will be introduced to researchers by the endocrinologist. Therefore, Participants will be chosen based on convenience sampling procedure Participants will be selected according to the following criteria:

**Inclusion criteria**

1) Age 40-60 at study entry

2) Men and women

3) Written and informed consent.

4) Patients must have an Endocrinologist that they have seen in every 3 months.

**Exclusion criteria**

1) Have other kinds of diabetes (type 1 and Gestational diabetes)

2) If they had been hospitalized

3) Lack of satisfaction could not collaborate or continue in the study.

4) Any current serious disorders determined to be clinically significant to the study.

**2.1.5 Sample size determination**

According to a meta-analysis study in diabetes interventions; Brown (1990), the required sample size, based on a power of 80% and a 2-tailed α of 0.05, was calculated 35 individuals per group. However, assuming a 10% loss to follow-up rate, we need 45 subjects per group to commence the trial.

**2.1.6 Statistical Analysis**

# Demographic characteristics among two groups will be compared using chi-square test and student’s t-test. In order to assess the effects of the group ACT intervention, differences between the two groups for glycated hemoglobin, self-care activities score and acceptance will be assessed, after controlling for pre-test scores on these variables and For this purpose, three one-way covariance analyses will be computed. Then, In order to assess the stability of the therapy, a repeated measures analysis of covariance with post-test and follow-up scores will be computed, controlling for pre-test effects. Finally, in order to evaluate the moderating role of coping styles in the relationship between group ACT with glycated hemoglobin, self-care activities and acceptance, three separate two-way analyses of covariance will be computed.

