## Study Overview

### 2.1.1 Methodology

Setting and Participants: The setting for this study will be the Endocrine Department of Labbafinejad Hospital in Tehran. The study will involve patients with type 2 diabetes. The study population will be male and female, in the age groups from 40 to 60. Sampling and Recruitment: Recruitment for the study will be facilitated by Labbafinejad Hospital. Participants will be introduced to researchers by the endocrinologist from the endocrine department. Interested parties will be encouraged to contact the psychologist directly and provide their name, phone number and preferred time of contact. Interested participants will be given an Information Kit, which will include: a sample consent form, a Backgrounder explaining the purpose of the study and contact list and phone numbers of the psychologist and researchers involved in the study.

Interested participants will be encouraged to ask questions to their Endocrinologist and directly to the Psychologist. The participants will be introduced to researchers by the endocrinologist from the endocrine department to participate in a 1-day educational workshop for self-management of diabetes,and all participants will be received a one-day workshop about diabetes control and will be encouraged to complete several questionnaires on socio-demographic characteristics, Summary of Diabetes Self-Care Activities (SDACA), Beck Depression Inventory, Acceptance and Action Diabetes Questionnaire and Brief COPE Questionnaire. then weight and height will be measured and blood samples will be obtained. Eligible participants will be randomly assigned to either the control or treatment groups (using the random number table), and will be booked for further appointment times.

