On subsequent visits, the intervention group patients will receive treatments including group acceptance and commitment therapy (ACT) for diabetes management in addition to the one day workshop. the ACT will be delivered during 10, 2-hour sessions. the control group patients will receive one day workshop to help diabetes control and they will be remained in a waiting list and will be received same treatment after the end of study (because of clinical ethical concern, but these result will not be entered into analysis). In one day workshop, both groups will be encouraged to engage in an active exercise routine. Both groups continue will be medications (e.g., Metformin), but they can be not changed medications and dosages during the study. Information of both groups will be obtained by questionnaires and results from blood tests at the points, before beginning therapy, after completing therapy sessions, and last, at a three-month follow-up. Blood test assessments will be provided for free as an incentive for participation.

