**2.1.2 Components of the Treatment**

The group acceptance and commitment therapy (ACT) will be delivered during 10, 2-hour sessions and each session of study is one week.

Across problems in living, ACT is a treatment that is difficult to deliver with integrity. The application of ACT to diabetes is no different, and contains specific challenges as well. The goal of the treatment is to compassionately assist patients in dealing with any thoughts, feelings, worries, anxieties, or fears they may have related to their disease and its maintenance in order to help them live their life in a valued direction related to their diabetes. A key first step in this holistic approach to diabetes self-management is to provide adequate information about how to care for one’s diabetes in order to address the specific motivational and acceptance pieces laid out in the treatment. Thus, the first half of the treatment provides specific information regarding the management of diabetes and the second half of the treatment addresses motivational and acceptance issues related to engaging in self-management behaviors. The treatment is divided into 5 main modules:

Module I: Education and Information

Module II: Food, Diabetes, and Your Health

Module III: Exercise and Diabetes

Module IV: Coping and Stress Management

Module V: Acceptance and Action

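### ACT is given in therapy groups, but the ANCOVAs and the sample size treat all patients as independent: if outcomes correlate within groups, type I error exceeds 5% and the 80% power is not assured

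*Protocol*

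**What the plan says.** Patients are randomised individually (section 2.1.1): "Eligible participants will be randomly assigned to either the control or treatment groups". The two arms are then handled differently. On the active side, section 2.1.2 states: "The group acceptance and commitment therapy (ACT) will be delivered during 10, 2-hour sessions". Its session table builds most sessions on sharing and discussion among group members. Controls attend the one-day workshop that both arms receive, after which "they will be remained in a waiting list" (section 2.1.1). They belong to no therapy group.

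Section 2.1.6 names the models. For glycated haemoglobin, self-care and acceptance, "three one-way covariance analyses will be computed" on the post-test, adjusted for the pre-test. A repeated measures ANCOVA on post-test and follow-up comes next, then three two-way ANCOVAs for moderation by coping style. Therapy group appears in none of them.

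Section 2.1.5 gives the sample size: "based on a power of 80% and a 2-tailed α of 0.05, was calculated 35 individuals per group". It is raised to 45 per arm to start, "assuming a 10% loss to follow-up rate". Sections 2.0 and 3.0 speak of 100 patients in total. No effect size, ICC, group size or number of groups is stated.

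**The concern.** Patients who share ten weekly sessions with the same people are likely to have outcomes more alike than those of patients in different groups. The design is therefore partially nested: clustered in the ACT arm, independent in the control arm. Every ANCOVA named assumes independent errors between patients. The repeated measures model handles correlation within one patient over time, not between members of one therapy group.

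With positive within-group correlation, the variance of the ACT mean is understated. Intervals are then too narrow, and the test rejects a true null more often than 5% of the time. This affects the between-arm comparison that the protocol names as its first purpose. The protocol itself fixes the models and the sample size, so this is not a detail simply left to an analysis plan. It also bears on conduct: the number of groups has to be planned, and membership is easiest to record as groups form.

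**Working it through.** **Inputs from the protocol.** Two-sided alpha 0.05, power 80%, 35 per arm, 45 per arm to start, 10% loss (section 2.1.5); 100 patients in total (sections 2.0 and 3.0).

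**Assumptions, none of them in the protocol.** 45 ACT patients in 5 groups of 9 or 3 groups of 15; ICC 0.01, 0.05 or 0.10; pre-post correlation 0.6; 45 evaluable per arm (50 started less 10%).

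**The plan's own figure.** No effect size is given, so 35 per arm cannot be reproduced, only inverted. With independent patients, d = (1.960 + 0.842) × √(2/35) = 0.67, or 0.68 with the t distribution. I use d = 0.68; it is back-solved, not a protocol figure. At that d with 45 evaluable per arm, power is 89% if patients are independent and baseline is not used.

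**Type I error of the planned ANCOVA.** With m patients per group, the ACT-arm variance is multiplied by DE = 1 + (m − 1) × ICC and the control arm is unchanged. With equal arms, the true standard error is √((1 + DE)/2) times the nominal one, and the actual two-sided error is about 2 × [1 − Φ(1.96/ratio)]. The ICC here is on the residual scale, after baseline adjustment.

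| Groups | ICC | DE | SE ratio | Error by formula | Error by simulation |
|---|---|---|---|---|---|
| 5 × 9 | 0.01 | 1.08 | 1.02 | 5.5% | 5.2% |
| 5 × 9 | 0.05 | 1.40 | 1.10 | 7.4% | 7.3% |
| 5 × 9 | 0.10 | 1.80 | 1.18 | 9.8% | 9.9% |
| 3 × 15 | 0.01 | 1.14 | 1.03 | 5.8% | – |
| 3 × 15 | 0.05 | 1.70 | 1.16 | 9.2% | 8.6% |
| 3 × 15 | 0.10 | 2.40 | 1.30 | 13.3% | 13.2% |

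The simulation fitted the planned ANCOVA with 45 per arm and correlation 0.6.

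**Power of a valid analysis.** Noncentral t with noncentrality d/SE and Satterthwaite degrees of freedom (k − 1 for k ACT groups, 44 for controls).

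Without baseline adjustment, SE = √((DE + 1)/45). Example, 5 groups at ICC 0.05: SE = √(2.40/45) = 0.231; noncentrality 0.68/0.231 = 2.94; df = 2.40²/(1.40²/4 + 1²/44) = 11.2; power 0.766.

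With adjustment, the residual variance is 1 − 0.6² = 0.64. If the ICC is on the residual scale, SE = √(0.64 × 2.40/45) = 0.185 and power is 0.92. If it is on the total-variance scale, the group component is not reduced: ACT variance 0.64 − 0.05 + 9 × 0.05 = 1.04, control 0.64, SE = √(1.68/45) = 0.193, power 0.89.

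| Groups | ICC | No adjustment | Adjusted, residual-scale ICC | Adjusted, total-scale ICC |
|---|---|---|---|---|
| 5 | 0.05 | 0.766 | 0.92 | 0.89 |
| 5 | 0.10 | 0.685 | 0.86 | 0.79 |
| 3 | 0.05 | 0.606 | 0.79 | 0.70 |
| 3 | 0.10 | 0.469 | 0.64 | 0.52 |

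If 45 per arm start, as in section 2.1.5, 10% loss leaves about 40. With 5 groups of 8 and no baseline adjustment, power is then 0.73 at ICC 0.05 and 0.65 at ICC 0.10.

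**The case against.** The strongest reply is that the harm depends on quantities the protocol does not give. At ICC 0.01 the inflation is negligible. The three outcomes need not share one ICC: glycated haemoglobin is a blood assay, while self-care and acceptance come from questionnaires. This stands, and it makes the finding conditional. A reader might infer that the standard errors are certainly wrong or that type I error certainly exceeds 5%. The documents support neither, because both require an ICC above zero.

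The second reply concerns power. Section 2.1.6 adjusts for the pre-test, and enrolment has slack: 35/0.9 is 39, yet 45 or 50 per arm are to start. A reader might take the unadjusted figures to mean that power falls below 80%. The documents do not support that either: with 5 groups and correlation 0.6, adjusted power is about 80% or more. A clear shortfall under adjustment appears only with 3 groups, and the 0.6 is itself assumed.

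The third reply is that a random group effect estimated from 3 groups is poorly determined, with about 3 to 5 degrees of freedom at ICC 0.05 to 0.10. That is true, and it is a reason to plan more groups.

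None of this rescues the planned test. Baseline adjustment and surplus patients can restore power, but they do not correct the type I error. Adding patients to the same groups raises m and therefore the design effect.

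**Conclusion.** The point holds in conditional form. The protocol describes a partially nested trial, but fixes models and a sample size that assume independent patients. If outcomes within therapy groups are correlated, standard errors are too small and type I error exceeds 5%. For 45 ACT patients in 3 to 5 groups, it is just above 5% at ICC 0.01, 7 to 9% at 0.05 and 10 to 13% at 0.10 (residual scale).

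For d = 0.68 and 45 evaluable per arm, power of a valid analysis at ICC 0.05 to 0.10 is 69 to 77% (5 groups) or 47 to 61% (3 groups) without baseline adjustment. With adjustment at correlation 0.6 it is about 79 to 92% or 52 to 79%. The 80% is therefore not assured, mainly if there are few groups. It has not been shown to be lost. The omission is certain; its size is not, because the ICC, number of groups, effect size and pre-post correlation are all assumptions.

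**What to change.** Plan several ACT groups rather than one or very few, state their number and size in the protocol, and record each ACT patient's group.

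For the between-arm analyses of glycated haemoglobin, self-care and acceptance (post-test, follow-up and moderator models), replace the ANCOVAs with baseline-adjusted partially nested mixed models. These carry a random therapy-group effect in the ACT arm only and use small-sample degrees of freedom (Satterthwaite or Kenward-Roger). Restate the power in section 2.1.5 with an explicit effect size, the number of groups and a range of ICCs.

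The cost is one extra data field and a different model. The downside is wider intervals on few degrees of freedom and a less favourable stated power. If all ACT patients form a single group, the group effect cannot be separated from the treatment effect. No model repairs that, and it must be stated as a limitation.

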***Purpose and benefits of the study***

This study has two purpose:1- To examine whether acceptance and commitment therapy works for participants with a diagnosis of type 2 diabetes and whether it provides clinically significant improvement in HbA1c reduction and improvement in self-management compared with the control group. 2- To assess the moderating role of coping styles in the relationship between acceptance and commitment therapy and self-management of patients with type 2 diabetes.

Perhaps the main contribution the study could give is that it opens up for other psychological modator and mediators in the effect of acceptance and commitment therapy on development of diabetes control. Therefore, this study may become important. this will be important information as many Mindfulness-Oriented Therapist already engaged in acceptance and commitment therapy

1. **PROPOSED STUDY**

This randomised controlled trial will evaluate the efficacy of acceptance and commitment therapy to effectively control diabetes. This will be an intervention trial using treatments and one-day educational workshop. The study sample will be randomised into two arms: treatment and control. The study population will consist of 100 patients with type 2 diabetes.

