# Justification of Methodology

The study trial shall involve 100 patients with type 2 diabetes as determined above. The trial shall last 22 weeks (10 weeks treatment time and 12 weeks follow-up) which we realized enough time to determine whether a clinically significant effect will be produced. We employed a randomized controlled design to determine if any change is significantly different from a control group not receiving the acceptance and commitment therapy. Control group allow us to determine if variability in diabetes control within individuals has overshadowed the impact of potential confounders. Examples of factors that could influence variability within individuals include age, sex, educational level, diabetes duration and medical treatment.

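### The only durability analysis named, a repeated-measures ANCOVA of post-test and follow-up, does not estimate the ACT-control difference at 3 months, and neither of its group terms shows whether the effect lasts

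*Protocol*

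**What the plan says.** Section 2.1.6 sets out three analysis steps. The first is a set of one-way ANCOVAs, one each for HbA1c, self-care and acceptance, adjusted for pre-test, to assess the effect of ACT. No occasion is named, but the order of the steps implies post-test. The second concerns durability and is also adjusted for pre-test: "In order to assess the stability of the therapy, a repeated measures analysis of covariance with post-test and follow-up scores will be computed". The third is a set of two-way ANCOVAs for moderation by coping style.

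The second step is the only one directed at whether the effect lasts. The section does not say which term of the model decides, what counts as stable, or that the arms will be compared at the 3-month follow-up itself.

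Section 2.1.5 gives the size of the main comparison as "based on a power of 80% and a 2-tailed α of 0.05, was calculated 35 individuals per group", on the authority of a cited meta-analysis and without an effect size. It continues: "assuming a 10% loss to follow-up rate, we need 45 subjects per group to commence the trial". The Justification of Methodology section gives another total: "The study trial shall involve 100 patients with type 2 diabetes as determined above". None of these figures is tied to the durability question.

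**The concern.** With two post-baseline occasions and two arms, the model offers two terms that involve the groups.

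- **Group-by-time** tests whether the ACT-control difference changed between post-test and follow-up. If a non-significant result were taken as stability, a trial too small to see fading would be credited with durability.
- **Group main effect** is the average of the post-test and follow-up differences. A large post-test effect can keep it significant when little or nothing remains at follow-up.

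Neither term estimates the effect at 3 months, which is what a reader of a durability claim wants to know. The Introduction faults earlier psychological interventions for working mostly over short periods, and 12 of the 22 trial weeks are follow-up, so the durability result will be read with interest.

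**Working it through.** **Inputs**

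- Two-sided alpha 0.05, 80% power, 35 evaluable per group (section 2.1.5).
- Completers per arm: 35 to 50. The lower end is the evaluable number in 2.1.5. The upper end is 100/2, assuming 1:1 allocation (the ratio is not stated). In between lie 45 × 0.9 = 40.5 and 50 × 0.9 = 45.
- Initial effect d: not stated. Assumption, back-solved below.
- Correlation r of post-test and follow-up given pre-test: not stated. Assumption, 0.5 to 0.9. Effects are in units of the pre-test-adjusted SD, taken as equal on both occasions.

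**The plan's own figure.** The 35 per group cannot be reproduced independently, because no effect size is given. Solving n = 2(1.96 + 0.84)²/d² for n = 35 gives d = 0.67; the t-test version gives 0.68. I use 0.68, so a halving is a loss of 0.34 SD.

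**Group-by-time.** This is a two-sample test on follow-up minus post-test, with SD = √(2(1−r)) and SE = SD × √(2/n). Power is from the noncentral t with one covariate.

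- n = 35, r = 0.5: SD = 1.00, SE = 0.239, 0.34/0.239 = 1.42, power 29%.
- n = 50, r = 0.7: SD = 0.775, SE = 0.155, 0.34/0.155 = 2.19, power 58%.

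Power to see the effect halve:

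| n per arm | r = 0.5 | r = 0.7 | r = 0.8 | r = 0.9 |
|---|---|---|---|---|
| 35 | 29% | 44% | 60% | 88% |
| 40 | 32% | 49% | 66% | 92% |
| 45 | 36% | 54% | 71% | 95% |
| 50 | 39% | 58% | 76% | 96% |

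A halving is therefore missed in 42-71% of trials at r = 0.5 to 0.7, 24-40% at 0.8 and 4-12% at 0.9. Total loss (0.68 SD) is seen with 80% power (n = 35) to 92% (n = 50) at r = 0.5, and with more at higher r.

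**Group main effect.** The mean of the two scores has SD = √((1+r)/2).

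- Effect halved: the average is (0.68 + 0.34)/2 = 0.51 SD, significant in 63-83% of trials (r = 0.5 to 0.7, n = 35 to 50).
- Effect gone: the average is (0.68 + 0)/2 = 0.34 SD. At n = 35, r = 0.7, SE = 0.922 × 0.239 = 0.220 and power is 33%. At n = 50, r = 0.5, SE = 0.866 × 0.200 = 0.173 and power is 49%.

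**What interval reporting would show.** The 95% CI half-width for the change in effect is 1.96 × SE. At r = 0.5 it is 0.47, 0.41 and 0.39 SD for n = 35, 45 and 50; at r = 0.7 it is 0.36, 0.32 and 0.30. For the follow-up difference alone it is 1.96 × √(2/n), or 0.47 SD (n = 35) to 0.39 SD (n = 50).

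**The case against.** The strongest reply is that the fault is inferred. A reader might take the protocol to say that a non-significant time or group-by-time term will be called stable. It does not: it names a model and a purpose and gives no rule. The deciding term and the reporting of intervals may be in an SAP that is not shown. This stands against any claim that the sponsor has adopted that rule. It does not remove the point, because section 2.1.6 does fix the model that is to answer the durability question, and neither group term of that model is the effect at follow-up.

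Three other stronger readings also fail.

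- **The test has low power.** Only conditionally. Effect size and correlation are assumed, power for a halving reaches 88-96% at r = 0.9, and total loss is usually seen by group-by-time. That term would also often flag the cases in which the averaged effect misleads.
- **Durability is a main aim.** The stated purposes are efficacy against control and moderation by coping style. Durability enters through the background and the follow-up period.
- **Patients missing one visit will be dropped.** A classical repeated-measures ANCOVA needs both scores, but the protocol does not say how a missed visit is handled, and an SAP could settle it. The power cost is small: going from 50 to 45 per arm at r = 0.5 lowers power from 39% to 36%. The remaining worry is selection, with 10% loss expected.

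It is also fair to say that the remedy adds no information. With complete data, the group-by-time test in a mixed model is essentially the same test.

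**Conclusion.** The point holds in a limited form. The protocol assesses durability through a model whose group terms are a change in effect and an average effect, and it names no estimate of the ACT-control difference at 3 months. Read on its own, either term can favour a conclusion that the effect lasts. Group-by-time does so when fading is partial and the correlation is about 0.8 or lower. The averaged effect does so even after total loss, in roughly a third to a half of trials at r = 0.5 to 0.7.

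These sizes rest on a back-solved effect of 0.68 SD, an assumed correlation, 1:1 allocation, equal SDs on both occasions and 35 to 50 completers per arm. That neither term is the follow-up effect depends on none of them. This is a worthwhile and inexpensive improvement to the analysis. It is not evidence that the sponsor intends to treat non-significance as stability.

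**What to change.** In section 2.1.6:

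1. Make the durability result the pre-test-adjusted ACT-control difference at the 3-month follow-up with its 95% CI, for each of the three outcomes.
2. Estimate it from a mixed model of post-test and follow-up scores with group × time and pre-test × time, using every randomised patient with any post-baseline value.
3. Report the change in effect from post-test to follow-up with its 95% CI from the same model.
4. State that stability will not be concluded from a non-significant time or group-by-time term.
5. State what each result supports. A follow-up interval excluding zero supports an effect still present at 3 months. It does not support an undiminished effect, because on the assumptions above a halved effect would itself exclude zero in 29-39% of trials (n = 35 to 50).

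The cost is wording only, as the data are already planned. The downside is that a durability claim becomes harder to make. The intervals show the imprecision without removing it: at r = 0.5 the interval for the change is wider than ±0.34 SD at every size considered, so an estimate of no change could not rule out a halving.
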